## Abstract

**Background:**

Each year, 1 million children develop TB resulting in over 200,000 child deaths. TB preventive treatment (TPT) is highly effective in preventing TB but remains poorly implemented for household child contacts. Home-based child contact management and TPT services may improve access to care. In this study, we aim to evaluate the effectiveness and cost-effectiveness of home-based contact management with TPT initiation in two TB high-burden African countries, Ethiopia and South Africa.

**Methods:**

This pragmatic cluster randomized trial compares home-based versus facility-based care delivery models for contact management. Thirty-six clinics with decentralized TB services (18 in Ethiopia and 18 in South Africa) were randomized in a 1:1 ratio to conduct either home-based or facility-based contact management. The study will attempt to enroll all eligible close child contacts of infectious drug-sensitive TB index patients diagnosed and treated for TB by one of the study clinics. Child TB contact management, including contact tracing, child evaluation, and TPT initiation and follow-up, will take place in the child’s home for the intervention arm and at the clinic for the control arm. The primary outcome is the cluster-level ratio of the number of household child contacts less than 15 years of age in Ethiopia and less than 5 years of age in South Africa initiated on TPT per index patient, comparing the intervention to the control arm. Secondary outcomes include child contact identification and the TB prevention continuum of care. Other implementation outcomes include acceptability, feasibility, fidelity, cost, and cost-effectiveness of the intervention.

**Discussion:**

This implementation research trial will determine whether home-based contact management identifies and initiates more household child contacts on TPT than facility-based contact management.

**Trial registration:**

NCT04369326. Registered on April 30, 2020.

**Supplementary Information:**

The online version contains supplementary material available at 10.1186/s13063-023-07514-7.

## Background

Tuberculosis (TB) and HIV remain among the top10 causes of child mortality in sub-Saharan Africa [1]. Each year, 1 million children develop TB resulting in over 200,000 child deaths [2]. TB preventive treatment (TPT) is highly effective, preventing >90% of TB disease among children adherent to treatment [3], but remains poorly implemented. In 2018, the UN High-Level Meeting on TB set ambitious targets to enhance TPT implementation [4]. Only 1.6 million household contacts less than 5 years of age (40% of target) and 600,000 household contacts 5 years and older (3% of target) were initiated on TPT from 2018 to 2021 [2]. The majority of household child contacts are either not identified or not linked to facility-based care, despite decentralized services [5, 6]. The World Health Organization (WHO) now endorses several short-course combination TPT regimens for household contacts, including 3HP (12 weekly doses of rifapentine and isoniazid) and 3RH (3 months of daily rifampicin and isoniazid) [7]. Both regimens hold promise for improved acceptability and treatment completion. Their effectiveness, however, will depend on improved implementation of contact management.

One third of TB-exposed children live in sub-Saharan Africa, where TB and HIV are syndemic. Children living with HIV are at higher risk of TB disease and suffer a disproportionate amount of TB-related mortality [8–11]. In 2021, more than 20,000 children living with HIV died of TB disease [12]. Children exposed to HIV may also be at higher risk of TB exposure, given adults in their household may also be living with HIV. Gaps throughout the HIV care continuum also limit the effectiveness of ART and have resulted in 160,000 new pediatric HIV infections and 97,000 AIDS-related child deaths in 2021 [13]. Through TB prevention services, we may be able to target and enhance access to pediatric HIV testing and prevention services among these high-risk children.

The World Health Organization (WHO) currently recommends household contact investigation for people newly diagnosed with TB in low- and middle-income countries, with an emphasis on pediatric contacts [14]. Although the aim of this policy has been to find previously undetected TB patients and reduce transmission, such investigations represent a missed opportunity to also start contacts without TB on TPT. WHO guidelines do not address the optimal implementation of TB contact investigation [14, 15]. The standard of care in most settings, or passive referral of pediatric contacts to the clinic by the index TB patient, has largely remained unsuccessful in practice. Implementation strategies to inform optimal implementation of contact management, which comprises contact investigation and TPT initiation and follow-up, among household child contacts less than 15 years are needed.

Community-based care delivery models for combined TB and HIV prevention may improve access to care for both services. Home-based contact tracing identifies more children under 5 years of age [6, 16]. The simplification of the pediatric screening process to a symptom-based approach allows for the possibility of home-based contact investigation and TPT initiation for asymptomatic children with referral of all symptomatic children. Integrated community-based pediatric TB and HIV prevention services, using existing community-based health teams in Ethiopia and South Africa, could improve access and reduce delays in the diagnosis, treatment, and prevention of TB and HIV in children. Furthermore, integrating these services into existing community-based services could make this approach cost-effective.

Few studies have evaluated the effect of home-based contact management on TPT uptake and completion in household child contacts [17, 18]. In this study, we aim to evaluate the effectiveness and cost-effectiveness of home-based contact management in two TB high-burden African countries.

### Objectives and endpoints

The primary objective of this study is to determine the effectiveness of home-based contact management, including TPT initiation and follow-up, using community-based healthcare workers to increase TPT initiation as compared to facility-based contact management. The primary endpoint is the cluster-level ratio of the number of household child contacts less than 15 years of age in Ethiopia and less than 5 years of age in South Africa initiated on TPT (3HP, 3RH, or 6H) per index patient, comparing the intervention to the control arm (Table 1). Because we anticipate heterogeneity in the epidemiology of TB and potential differences in the response to the intervention between countries, the primary outcome will be assessed across countries and within countries.

**Table 1 Tab1:** Primary and secondary outcomes for the CHIP-TB trial

**Primary outcome**	**Outcome description**	
TPT initiation among child contacts	The cluster-level ratio of the number of household child contacts less than 15 years of age in Ethiopia and less than 5 years of age in South Africa initiated on TPT per index patient, comparing the intervention to the control arm	
**Secondary outcome**	**Outcome description**	
Child contact identification	The cluster-level ratio of the number of household child contacts less than 15 years of age in Ethiopia and less than 5 years of age in South Africa identified per index patient	
Continuum of care	The cluster-level proportions of estimated child contacts who progress through each stage of the pediatric TB prevention continuum of care (identification, screening, initiation, and completion) overall and by age, by TPT regimen, and by country. *estimated child contacts will be calculated using DHS data	
Treatment completion (as defined by WHO TPT Handbook)	• Proportion of children initiated on TPT who successfully completed TPT • Proportion of children initiated on TPT who were lost to follow-up • Proportion of children initiated on TPT with incident TB (treatment failure) • Proportion of children initiated on TPT who died • Proportion of children initiated on TPT who discontinued TPT due to: toxicity, drug-drug interaction, severe illness (e.g., malaria), pregnancy, or family preference *Treatment completion was defined as 11 doses in 16 weeks for 3HP and 68 doses in 4 months for 3RH [19].	
**Implementation outcome**	**Quantitative assessment**	**Qualitative assessment**
Acceptability of home-based contact management to all stakeholders (CG, HEW, TBF, PM)	• Proportion of identified households who agree to a home visit • Proportion declining HIV testing (South Africa only) • Proportion of children HIV tested by the community health team • Proportion of newly diagnosed HIV-positive children who are referred to the clinic for ART initiation	• Individual in-depth interviews (CG, HEW, TBF, PM)
**Fidelity** to the home-based contact management strategy	• Proportion of children initiated on the correct TPT regimen • Proportion of children initiated on the correct TPT dose	• Individual in-depth interviews (CG, HEW, TBF, PM)
**Feasibility** of home visits for CGs and community-based health teams	• Average number household visit attempts per household • Mean and median duration of each household visit • Proportion of index patients who refuse to provide an address or who provide an invalid/incorrect address	• Individual in-depth interviews (CG, HEW, TBF, PM)
**Cost and cost effectiveness**	• Mean difference in total patient and health system costs between the intervention and control arms • Incremental cost-effectiveness ratio (ICER) where effectiveness is modeled as the number of disability adjusted life years (DLYs) averted by the intervention in comparison with the standard of care.	• Structured interviews to assess implementation costs • Time and Motion observations of TB preventive care

Stakeholders: *CG* Caregiver, *HEW* Health extension worker, *TBF* TB focal persons, *PM* Program manager

The secondary objectives of the study are to evaluate: (1) the TPT continuum of care by country, TPT regimen (3RH and 3HP), and age (< 5 and 5–14 years); (2) acceptability, feasibility, and fidelity of home-based contact management and HIV preventive services in each setting; (3) TPT treatment outcomes, including tolerability and reported adherence; and (4) the cost-effectiveness of home-based versus facility-based child contact management (Table 1).

Data will be collected on staffing changes within the TB clinic and community health teams and stockouts of TPT medications, pyridoxine, and other supplies needed for pediatric contact management (specimen collection, file and registers, etc.), to understand trends in the data.

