### Sample size considerations

We considered sample size estimation for the South Africa and Ethiopia sites separately because of the differences in TB epidemiology in the two countries. Sample size calculations were based on the primary outcome which is the clinic-level number of child contacts under age 15 years (Ethiopia) or under 5 years (South Africa) initiating TPT per index patient, compared between the two study arms. We expect there to be a harmonic mean of 51 and 32 diagnosed TB patients per clinic during the study period, in South Africa and Ethiopia respectively. We also expect 20% refusals, withdrawals, or loss to follow-up leading to an average of 40 and 26 TB patients, as reported by the respective TB programs. An estimate of the coefficient of variation (CV) was obtained from a previous contact tracing study in South Africa which was 0.35 [6]. We assumed a similar amount of between-cluster variability in Ethiopia, and we also evaluated how the required sample size changed if we considered a slightly higher CV of 0.4. Prior household-based contact tracing studies and 2016 DHS data showed that households of index TB patients in South Africa and Ethiopia, respectively, have 1.8 and 2.1 children under the age of 15, and we expect that 30% would initiate TPT under the standard of care [6, 29–32]. We hypothesize that the intervention would double the number of children per TB patient initiated on TPT — from 0.5 (=1.8×0.3) to 1 in South Africa, and 0.6 (=2.1×0.3) to 1.2 in Ethiopia. A total of 18 (9 per arm) clinics in each country would be required to detect this effect with 80% power at a 5% level of significance assuming a CV of 0.35. A larger CV of 0.4 would require 20 and 22 clinics in South Africa and Ethiopia, respectively.

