### Statistical analysis

#### Primary and secondary outcome analyses

Summary statistics of the enrolled index patients will be presented stratified by arm and study site. Analysis of the primary outcome of the number of child contacts less than of 15 years of age in Ethiopia and less than 5 years of age in South Africa who initiate TPT per index patient diagnosed will be stratified by country. Cluster-level ratios will be compared between arms using an unpaired t-test which has been shown to be robust for a relatively small number of clusters [24]. The ratio of the study arm mean ratios and the corresponding 95% confidence interval will be calculated. A log-transformation of the cluster-level ratios will be applied before applying the *t*-test if the outcomes are highly skewed. If the number of index patients varies substantially between clinics, weighted (by clinic size) mean ratios will be used. If the sample size allows, we will compare the numbers of children started on TPT between arms stratified by TPT regimen (3HP vs 3RH) and children’s age groups (^3^5 vs <5 for Ethiopia).

Secondary outcomes to be compared between arms will be the number of child contacts identified (using index patient’s clinic-based contact tracing report, the child contact management file, and the community-level file maintained by the community health team) per index patient, and the proportions of these who are screened, initiated on TPT and who complete TPT. As done for the primary outcome, cluster-level summaries for secondary outcomes will also be compared between arms. Count outcomes will be compared using Poisson regression, and cluster-level proportions (after a log-transformation, if necessary) will be compared using a *t*-test.

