We will provide summary statistics of TPT completion rates and losses to follow-up discontinuation (due to incident TB, side effects, transfer out, other reasons, or death) stratified by study arm and site. TPT completion will be defined as three monthly follow-up visits over a 4-month period (3HP or 3HR) or six monthly visits over a 9-month period (6H). Loss to follow-up will be defined as no return visit within three months of the child’s last recorded visit. Other reported outcomes will include new HIV diagnoses among children who are referred for ART initiation. All outcomes will be summarized by the study arm, and formal statistical tests will be conducted if the number of events observed allows. All data will be abstracted by study staff from index patient and child contact management files.

Acceptability of the intervention will be assessed as the proportion of child contacts who are identified and whose families agrees for them to be screened by community-based clinic staff (community health worker, professional nurse, type of provider dependent on the setting) in their home. We will also summarize reasons for the refusal of a household visit in the intervention arm using proportions among those approached. Fidelity to guidelines will be summarized as the proportion of TB contacts initiated on the correct TPT regimen by age and HIV status, and the proportion of TPT initiations with the correct dose for weight to measure guideline fidelity of community-based TB preventive care.

Process outcomes to be reported will include drug shortages and stockouts, stockouts of supplies needed for pediatric specimen collection, stockouts of TB and contact file and registers, other materials needed for the intervention (scale, etc.), staffing within the TB clinic and community health teams, use of community health teams to do contact tracing in control clinics, changes in key personnel including community health workers and TB nurses, and time the TB nurse and/or community health worker is pulled away from TB activities.

All analyses will be conducted using STATA software (StataCorp. 2021) [25].

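### TPT completion may be tested between arms among started children or identified contacts, two groups whose make-up the intervention is expected to change

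*Protocol article*

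**What the plan says.** Table 1 (Objectives and endpoints) lists Treatment completion as a secondary outcome made up of five proportions. The first is "Proportion of children initiated on TPT who successfully completed TPT" and the second is "Proportion of children initiated on TPT who were lost to follow-up". Incident TB, death and discontinuation follow on the same denominator.

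Completion appears in two further places, each with a different denominator:

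- Table 1, Continuum of care: the "cluster-level proportions of estimated child contacts who progress through each stage", from identification to completion, with the note that "estimated child contacts will be calculated using DHS data".
- Primary and secondary outcome analyses: the outcomes named for comparison are contacts identified per index patient, and then the share of those identified contacts who are screened, start TPT and complete it.

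On testing, the same section says that "cluster-level summaries for secondary outcomes will also be compared between arms", with a t-test for proportions. It then promises summary statistics of completion, loss and discontinuation by arm and site, and ends by saying of all outcomes that "formal statistical tests will be conducted if the number of events observed allows".

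On starting TPT, Sample size considerations says: "We hypothesize that the intervention would double the number of children per TB patient initiated on TPT". The standard-of-care level is taken as 30% of contacts.

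**The concern.** Starting TPT is the primary outcome. It happens after randomisation and is the step the intervention is built to change. The Background says that leaving the index patient to bring children to the clinic has mostly failed. Control starters are therefore largely children whose families came to a clinic, while home starters also include children whose families would not have come. The two groups can differ in how likely they are to finish, whatever the care they receive. Identified contacts have the same weakness, because identification is itself a secondary outcome that home visits are expected to raise.

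At stake is the reading of a secondary result. The trial could report that home-based care lowers completion when more children per index patient finish TPT. A gap in case mix could also hide a true benefit of home follow-up, or create an apparent one.

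**Working it through.** **1. The plan's own figures.** Starts per index patient under standard of care: 1.8 × 0.30 = 0.54 in South Africa (given as 0.5) and 2.1 × 0.30 = 0.63 in Ethiopia (given as 0.6). These reproduce up to rounding. Doubling gives 1.0 and 1.2, that is, 30% to 60% of contacts. With 40 and 26 index patients per clinic, starters per clinic are 40 × 0.5 = 20 against 40 × 1.0 = 40 in South Africa, and 26 × 0.6 ≈ 16 against 26 × 1.2 ≈ 31 in Ethiopia. The 9 clinics per arm do not come back exactly: the Hayes–Bennett formula at 80% power and CV 0.35 gives 6.98 and 7.32, so 7 and 8. That does not bear on this point, and 9 per arm is used below.

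**2. Who the home starters are.** Assume that every child who would start under control would also start under home care. The share of home starters who would not have started under control is then (0.60 − 0.30)/0.60 = 50%.

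**3. Completion by denominator.** Let pA be completion in children who would start in either arm and pB completion in those started only at home. Neither is in the documents; both are assumed. Let the arm have no effect on any child's own chance of finishing.

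- Among starters: control pA; home (0.30 pA + 0.30 pB)/0.60 = (pA + pB)/2. Difference: (pB − pA)/2.
- Over all contacts: control 0.30 pA; home 0.30 pA + 0.30 pB. Difference: 0.30 pB, which is positive whenever any added starter finishes.

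| pA / pB (assumed) | Starters: control, home (difference) | All contacts: control, home (difference) |
|---|---|---|
| 85% / 65% | 85%, 75% (−10) | 25.5%, 45.0% (+19.5) |
| 85% / 75% | 85%, 80% (−5) | 25.5%, 48.0% (+22.5) |
| 85% / 85% | 85%, 85% (0) | 25.5%, 51.0% (+25.5) |
| 75% / 85% | 75%, 80% (+5) | 22.5%, 48.0% (+25.5) |

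**4. What a test among starters would do.** An unpaired t-test on clinic proportions was simulated with 9 clinics per arm, the starters per clinic from step 1, a two-sided 5% level and 20,000 runs. The between-clinic SD of completion on the logit scale was varied from 0 to 0.8 (assumed). The chance that home care is declared significantly worse is:

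- 85% / 65%: 25–65% in Ethiopia, 27–77% in South Africa.
- 85% / 75%: 10–24% in Ethiopia, 11–30% in South Africa.
- 85% / 85%: about 2.5–3%, the nominal level in that direction.
- 75% / 85%: below 1%. Here the bias favours home care; in a separate run with Ethiopian inputs and a clinic SD of 10 percentage points, home care was significantly better in 10% of trials.

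The South African starter counts rest on children under 15, although only those under 5 are enrolled there, so they are probably too high. With about a third as many (7 against 14), the 85% / 65% case gives 21–38%.

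**5. Identified contacts as denominator.** In the 85% / 65% case, completed courses per contact rise by a factor of 45.0/25.5 = 1.76. If identification also doubled (an assumption), completion over identified contacts would change by a factor of 1.76/2 = 0.88. That is a relative fall of 12%, while 76% more courses are completed.

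**The case against.** The strongest reply is that the plan does not rest completion on starters alone. A reader of the Treatment completion row might infer that it does, but the documents do not support this: the Continuum row gives completion over estimated contacts, and the analysis section names identified contacts. If the survey figure is a fixed number of children per household applied to index patients (Table 1 does not say how it is used), completion per estimated contact is simply completions per index patient divided by a constant. This stands, and it is why the remedy is small. It does not settle the point, because the one completion proportion spelled out for comparison uses identified contacts, and the general sentence on secondary outcomes does not say which denominator governs.

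Second, the treatment outcomes are introduced as summary statistics, and tests are conditional. This also stands: a test among starters is permitted and is not named for completion. But completion is likely to be the commonest of the five outcomes, so the condition would be met easily, and nothing marks these proportions as descriptive only.

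Third, loss, toxicity and discontinuation can occur only in a child who started, and per index patient they would rise merely because more children start. This stands in full: starters are a sensible population for describing these outcomes, and the proportions should be kept.

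Fourth, every completion rate above is assumed, and monthly home follow-up might raise completion. This stands as a limit on size and direction. It is no defence of the test, since a difference in case mix could mask that benefit just as well.

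Finally, the article condenses a fuller protocol, and caveats of this kind are often left to the analysis plan. The point concerns only what the article states: the denominators, the comparison between arms and the permission to test.

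**Conclusion.** The concern holds in a limited form. The five proportions among starters, and completion among identified contacts, use denominators formed after randomisation that the intervention is expected to change, and the analysis section provides for comparing and testing them between arms. Only the Continuum row has a denominator that does not depend on arm, provided the same survey figure is applied in both arms, and the analysis section does not take it up.

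The size is conditional. With 85% and 65% completion assumed, the sign reverses with the denominator: −10 points among starters, +19.5 over all contacts. A test among starters then shows home care significantly worse in roughly 25–77% of trials at the planned numbers, although no child does worse. With equal completion the problem vanishes, and with 75% and 85% it favours home care. A reader might infer that the home arm will look worse; the documents contain no completion rate and do not support that. This is a matter of secondary outcomes and does not touch the primary comparison.

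**What to change.** In Primary and secondary outcome analyses, make the between-arm test of completion the clinic-level number of children completing TPT per index patient (or per estimated contact, as in the Continuum row), analysed like the primary outcome. State that the five proportions among starters are reported by arm as descriptive, without p-values, because starters are not a randomised comparison, and exclude them from the sentences that provide for comparison and formal tests. Treat the proportion of identified contacts who complete in the same way.

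The cost is wording only: the data and the method are already in the plan. The downside is that there will be no p-value for completion among starters.
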